### Outcome assessment

Measures will be conducted immediately before randomisation (baseline), and at 3 months and 6 months post-randomisation (table 3).

**Table 3 T3:** MOSAIC trial summary of measures

Measure	Administered by	Baseline	3 months	6 months
Baseline measures				
Sociodemographic characteristics	Self			
San Diego Claudication Questionnaire	Self			
Ankle-Brachial Pressure Index	Researcher			
Body mass index	Researcher			
Primary outcome				
6 min walking distance	Researcher	X	X	
Secondary outcomes				
Pain-free walking time	Researcher	X	X	
Maximal walking time	Researcher	X	X	
Self-reported maximal walking distance*	Self	X	X	X
Walking Estimated-Limitation calculated by History	Self	X	X	X
Nottingham Extended Activities of Daily Living scale	Self	X	X	X
Vascular Quality of Life-6*	Self	X	X	X
EQ-5D-5L	Self	X	X	X
Brief International Physical Activity Questionnaire*	Self	X	X	X
Client Services Receipt Inventory	Self	X	X	X
Process measures				
Brief Illness Perceptions Questionnaire	Self	X	X	X
Theory of Planned Behaviour Questionnaire	Self	X	X	X
Action Planning and Action Control	Self	X	X	X
Exercise Adherence Rating Scale	Self		X	X
Adverse events*	Self/physiotherapist/ researcher		X	X

*Minimum dataset.

MOSAIC, MOtivating Structured walking Activity in people with Intermittent Claudication.

### Data collection

Written informed consent will be obtained prior to any data collection. Baseline and 3-month follow-up measures will be conducted face to face by an independent assessor who will attend each site. At 6 months, the outcomes will be collected either electronically or via a standard postal questionnaire pack (with prepaid return envelope).

Data will be collected and stored using a secure database system. Participants opting to complete self-reported assessments electronically will be provided with a unique username and password to log onto the database and complete measures either during the face-to-face appointment (baseline and 3 months) or from home (at 6 months). Any research data completed by pencil and paper will be entered to the secure database by the independent outcome assessor or trial research assistant.

At 3-month follow-up, participants who are unable or refuse to attend an appointment to complete the primary outcome will be invited to complete the secondary outcomes at home either electronically or by post.

Attrition will be minimised via standardised text, email and telephone reminders. Following these, if no data have been returned, the assessor will telephone the participant to collect a minimum data set (table 3).

### Baseline measures

At baseline, participants will complete a bespoke sociodemographic and clinical characteristics questionnaire (including age, sex, smoking history, comorbidities and claudication symptom classification (San Diego Claudication Questionnaire^34^). Standard measures of body mass index and Ankle-Brachial Pressure Index^37^ will also be determined in addition to the outcomes detailed below.

### Primary outcome

The primary outcome is the difference in mean 6MWD in metres at 3 months between groups. This will be assessed by a self-paced 6 min walk test over a 60.96 m (200 foot) circuit.^38–40^ Pain intensity will be measured before and after the walk test using a standardised pain scale for claudication.^41^ The walk test will be completed twice, with the highest 6MWD used for analysis.

### Secondary outcome measures

Other measures will be used to assess the broader effects of the MOSAIC intervention.

Maximal walking ability (duration walked before resting (seconds)) and pain-free walking ability (duration walked before reported pain onset (seconds)) will be recorded during the 6 min walk test.^42 43^ These parameters evaluate the global and integrated physiological responses of all systems involved with exercise and symptom manifestation.

Self-reported maximal walking distance (SR-MWD) will be measured by one global item: ‘What is the maximum distance (in metres) you can walk at your usual pace on a flat surface before leg pain forces you to stop?’^44^ and the 4-item Walking Estimated-Limitation Calculated by History questionnaire (WELCH).^45 46^

Nottingham Extended Activities of Daily Living scale (NEADL)^47 48^ is a 22-item measure with 4 subscales (mobility, kitchen tasks, domestic tasks and leisure activities) and will assess function.

The 6-item disease specific Vascular Quality of Life Questionnaire-6 (VascuQol-6)^49^ and the EQ-5D-5L will assess QoL.^50^

The 7-item Brief IPAQ will estimate daily physical activity.^35^

Adverse events will be recorded by asking participants a single open-ended item: ‘Have you had any problems since your last assessment?’ at 3 and 6-month follow-up. Trial physiotherapists will also report any adverse events in participants randomised to receive the MOSAIC intervention.

To determine the MCID, participants will provide a global rating of change score after five measures (6MWD, SR-MWD, WELCH, NEADL and VascuQoL-6) at the 3 and 6-month follow-up assessments. In response to the question: ‘Has there been any change in your walking ability/walking distance/daily activities etc since the last test?’ participants will be asked to rate their perceived change on a transitional three-point scale (1, worse; 2, about the same; 3, better). If they indicate no change, the participant will score 0. If they indicate there has been an improvement or deterioration, they will be asked to score their change on a 15-point Likert scale: (−7=a very great deal worse to 7=a very great deal better). Scores of −1, 0 and 1 will be considered no change, scores of 2–3 small improvement and scores of 4–7 substantial improvement.^51 52^

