### Interventions

### MOtivating Structured walking Activity in people with Intermittent Claudication

Participants randomised to the intervention group will receive the MOSAIC intervention in addition to the usual care provided by their direct care team.

MOSAIC aims to increase an individual’s walking ability. It comprises two 60 min face-to-face consultations (weeks 1 and 2) and two 20 min follow-up telephone calls (weeks 6 and 12). The content of each session is standardised and incorporates 15 behavioural change techniques, but sessions may be tailored based on participants’ knowledge, goals, symptoms and current walking (tables 1 and 2). Walking plans will be agreed collaboratively between the participant and the physiotherapist and include progressive, individualised targets for walking frequency, intensity and duration to achieve recommendations (30–50 min of walking three times/week at an intensity that elicits pain within 3–5 min).^6^ MOSAIC is supplemented by an interactive participant manual, containing worksheets and a walking diary, and by a pedometer.

**Table 1 T1:** Format and content of the MOtivating Structured walking Activity in people with Intermittent Claudication (MOSAIC) intervention

1. Session 1 (60 min face to face)	2. Session 2 (60 min face to face)

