### Physiotherapist training and supervision

The MOSAIC sessions will be delivered by experienced physiotherapists (band 6 and above) who will be trained in motivational interviewing and behavioural change techniques. All trial physiotherapists will receive 2 days training on the trial objectives, research processes, underpinning psychological theories and MOSAIC intervention content, delivery and materials. Trial physiotherapists will be explicitly instructed on how to identify and report any adverse events and about the risks and consequences of contamination. Training will be delivered by the trial team (LB, JW, MGH, JB, GF and BV) and an accredited provider of motivational interviewing training ([name] Consultancy). A bespoke manual will support training and delivery of MOSAIC and includes an intervention checklist for each session.

To promote consistency of intervention delivery, all face-to-face and telephone sessions will be audiorecorded and individualised feedback on at least one of the first face-to-face and telephone MOSAIC sessions will be provided to each physiotherapist by a member of the trial team (LB and BV). Physiotherapists will record each session on a checklist (eg, duration, content), which will be reviewed by members of the trial team for adherence to the intervention. The trial physiotherapists will attend regular meetings supervised by members of the trial team (JW, LB and BV) to maintain skills and receive feedback and support.

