### Usual care

Participants randomised to the comparison group will continue to receive usual care provided by the NHS for intermittent claudication. Usual care is typically delivered in the vascular outpatient clinic by a vascular surgeon or specialist nurse and may include: the provision of information about PAD and lifestyle modifications (eg, smoking cessation, diet and weight management), supervised exercise, risk factor management including lipid modification, statin therapy and antiplatelet therapy, pharmacotherapy to improve leg function (vasodilators such as naftidrofuryl oxalate) or revascularisation (eg, angioplasty, stenting and bypass).^7^ Participants may seek concomitant treatment during the trial if they wish to. Any other treatments accessed by participants, (eg, from their general practitioner/other health professionals), will be recorded on a modified Client Service Receipt Inventory^36^ at follow-up.

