### Statistical analysis

A statistical analysis plan will be written by the trial statistician (SE) and agreed with the trial management group and joint trial steering committee/data monitoring and ethics committee. Analyses of primary and secondary outcomes and process variables will be conducted on an intention-to-treat basis and all included participants will be analysed as randomised.

The primary outcome will be analysed using multiple regression and adjusted for baseline 6MWD and site. Results will be reported as the difference in mean 6MWD between the intervention and control groups with 95% CIs. Other continuous outcomes and process variables will be similarly analysed. If appropriate, a mediation analysis using linear regression will examine mechanisms of impact.

Descriptive statistics for sociodemographic and clinical characteristics, attendance at MOSAIC sessions, adherence to treatment and referral to or uptake of other treatments will be computed. Adverse events and serious adverse events will be described.

To determine the MCID, change scores for the five clinical measures will be calculated by subtracting the baseline result from the follow-up results for each participant. Correlations will be computed for participant self-assessment of performance scores and change in clinical outcomes. The mean change in scores for participants reporting no change, small improvement and substantial improvement will be compared by analysis of variance. The sensitivity and specificity for change in score to distinguish participants classified as changed (≥2) from those whose performance was unchanged (−1 to +1) will be calculated and a receiver operating characteristic curve obtained.^62^ The data point corresponding to the upper left corner of the curve will represent the MCID.

As a sensitivity analysis, the MCID will be also calculated using a distribution-based approach. The SE of measurement for all participants scores will be used to estimate the MCID based on the following equation: $\sigma_{1}\surd (1-r)$ where $\sigma_{1}$ is the baseline SD and r represents the intraclass correlation coefficient, which is a measure of the test–retest reliability of the scale. The intraclass correlation coefficient will be calculated using the baseline and follow-up scores for each participant. Using this method, 1 SE of measurement represents the estimated MCID.^63^

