## Ethical considerations and dissemination

Approvals were provided from the Research and Development departments at all participating sites. The chief investigator will submit and, if required, obtain approval from relevant parties for all substantial amendments to the original approved documents.

The trial will be completed in accordance with the Declaration of Helsinki, the International Conference for Harmonisation of Good Clinical Practice guidelines and the Research Governance Framework for Health and Social Care.

King’s College London and Guy’s and St Thomas’ NHS Foundation Trust (R&[contact]) are the trial sponsors and the lead site (Guy’s and St Thomas’ NHS Foundation Trust) will monitor and audit this project to ensure compliance with the necessary legislation.

This is a low risk trial because MOSAIC is a non-invasive treatment which will be delivered by trained, registered physiotherapists. Any adverse events will be recorded by the trained, trial physiotherapists and reported to the trial team. Participants will also be offered the opportunity to report any adverse events at follow-up assessments. Any serious adverse events will be referred to the chief investigator immediately.

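### Physiotherapists report adverse events in the MOSAIC arm only, so an all-source description by arm would be tilted against MOSAIC, mainly for non-serious events in the first 3 months

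*Protocol article*

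**What the plan says.** Adverse events appear among the secondary outcomes (Protocol article, Secondary outcome measures). For both arms the method is the same: "Adverse events will be recorded by asking participants a single open-ended item", put at the 3- and 6-month follow-up. The same paragraph adds a source for one arm: "Trial physiotherapists will also report any adverse events in participants randomised to receive the MOSAIC intervention".

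Other sections show how far that source reaches:

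- **Contacts.** The Interventions section gives MOSAIC participants two face-to-face sessions (weeks 1 and 2) and two telephone calls (weeks 6 and 12).
- **Training.** Under Physiotherapist training and supervision: "Trial physiotherapists will be explicitly instructed on how to identify and report any adverse events".
- **Usual care.** "Participants randomised to the comparison group will continue to receive usual care provided by the NHS for intermittent claudication"; no scheduled contact with a trial physiotherapist is described.
- **Masking.** Under Randomisation, blinding and allocation concealment, the outcome assessor is masked. The physiotherapists and the participants are not.
- **Safety route.** Ethical considerations and dissemination says "Any adverse events will be recorded by the trained, trial physiotherapists and reported to the trial team". It adds that participants can report events at follow-up, and that any serious adverse event goes to the chief investigator at once. That last statement is not limited to one arm.
- **Table 3.** It names participant, physiotherapist and researcher as sources, without saying that one of them exists in one arm only. It also places adverse events in the minimum dataset.

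On analysis, the Statistical analysis section says only: "Adverse events and serious adverse events will be described".

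**The concern.** Adverse event counts in a two-arm trial are read across the arms, even when no test is planned. Here one arm has an extra route by which an event can enter the record. That route is operated by unmasked staff who deliver the treatment and have been told to look for events. If the arms had identical true rates, a table that counted events from any source would tend to show more of them under MOSAIC. A reader could take that as harm from walking exercise, or a real safety advantage of MOSAIC could be hidden. The collection rule is stated in the article itself, so the issue does not depend on what the unseen statistical analysis plan contains. That plan can separate the sources only if the source of each report was recorded.

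**Working it through.** The article gives no adverse event rate, no capture rate and no adverse event ratio, so there is no stated figure to reproduce. The direction can be derived. The size can only be illustrated.

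**Inputs from the article.** 96 participants per group (Abstract); a common question at 3 and 6 months; physiotherapist contacts at weeks 1, 2, 6 and 12; 20% attrition at 3 months allowed for in the Sample size section.

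**Assumed inputs.** The true risk p is equal in both arms, with p = 20% used for counts. The share of events captured by the common question is s = 0.5, 0.7 or 0.9. The share of the events missed by the question that physiotherapists capture is q = 0.1, 0.3 or 0.5. Each affected participant is treated as having one event.

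**Formula.** Recorded in usual care: p·s. Recorded in MOSAIC from any source: p·[1 − (1 − s)(1 − q)]. The ratio is

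[1 − (1 − s)(1 − q)] / s = 1 + q(1 − s)/s.

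The risk p cancels. The ratio exceeds 1 whenever q > 0 and s < 1, and never falls below 1. So the direction follows from the design.

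**Ratio within the contact period (to about 3 months)**

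| s | q = 0.1 | q = 0.3 | q = 0.5 |
|---|---|---|---|
| 0.5 | 1.10 | 1.30 | 1.50 |
| 0.7 | 1.04 | 1.13 | 1.21 |
| 0.9 | 1.01 | 1.03 | 1.06 |

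As counts, 96 × 0.20 = 19.2 affected participants per arm:

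- s = 0.5, q = 0.5: MOSAIC 19.2 × 0.75 = 14.4; usual care 19.2 × 0.50 = 9.6.
- s = 0.7, q = 0.3: MOSAIC 19.2 × 0.79 = 15.2; usual care 19.2 × 0.70 = 13.4.
- s = 0.9, q = 0.1: MOSAIC 19.2 × 0.91 = 17.5; usual care 19.2 × 0.90 = 17.3.

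**Over 6 months.** No physiotherapist contact is scheduled after week 12. If events fall evenly in the two 3-month periods (an assumption), q applies to half of them and the ratio becomes 1 + 0.5·q(1 − s)/s. Then 1.50 becomes 1.25, 1.30 becomes 1.15, 1.13 becomes 1.06, and the smallest value stays at about 1.01.

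**If some participants never answer the question.** Suppose 20% per arm never answer, but those in MOSAIC are still seen by physiotherapists. The ratio is then {0.8[1 − (1 − s)(1 − q)] + 0.2q} / (0.8s). It runs from (0.728 + 0.02)/0.72 = 1.04 at s = 0.9, q = 0.1, to (0.60 + 0.10)/0.40 = 1.75 at s = 0.5, q = 0.5. This is a pessimistic case. The 20% is the allowance made for the walking test, whereas the adverse event question belongs to the minimum dataset, which the Data collection section says is gathered by telephone from non-responders.

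**The case against.** The strongest reply is that the article fixes how events are collected but not how they are tabulated. It promises description only, states no pooling and no between-arm test, and defers detail to a statistical analysis plan that could split events by source and period. This stands. A reader might infer that the plan pools all sources and that equal true rates are bound to look unequal. The article does not support that: an apparent excess needs an all-source table, incomplete capture by the question, and extra capture by physiotherapists. The tilt is therefore conditional on an all-source description, which the article leaves open.

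A reader might also infer that a usual-care event cannot reach the trial team before 3 months. The article describes no scheduled route for ordinary events in that period, but its statement that serious events are referred immediately applies to either arm, and site reporting procedures belong in the full protocol, which is not shown.

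Third, having the staff who deliver an intervention report events is ordinary safety oversight. That is right, and nothing here asks for it to stop.

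Finally, the common question is not a perfect yardstick. Participants know their allocation, and MOSAIC participants have discussed symptoms and barriers with a physiotherapist. This also stands: the question is the most symmetric source available, but it does not guarantee equal ascertainment.

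**Conclusion.** The concern holds in a limited form. Ascertainment of adverse events is unequal by a stated rule, and a description by arm using every source would be tilted against MOSAIC. The effect should sit mainly in non-serious events in the first 3 months. Serious events are probably less affected, on the assumption that participants recall them at follow-up or that they are referred as they occur.

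The direction rests only on the added source capturing something the question misses. The size rests wholly on assumed capture rates: a ratio of about 1.0 to 1.5 within the contact period, and about 1.0 to 1.25 over 6 months if events are spread evenly. At the middle setting the gap is under two participants per arm (15.2 against 13.4). It would be wrong to quote 1.5 as the expected distortion for the whole trial. The primary outcome and the sample size are not affected.

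**What to change.** 1. Record the source of each adverse event report (common question, physiotherapist, other), allowing more than one source per event.
2. Base the between-arm description of non-serious events on those elicited by the identical question at 3 and 6 months in both arms.
3. List events known only through physiotherapists separately, labelled as MOSAIC-only and non-comparative.
4. Report all serious adverse events and deaths by arm whatever their source, show the source, and state that ascertainment was unequal. Restricting these to the follow-up question would drop deaths and serious events in participants who cannot answer it.

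The cost is one field on the adverse event form and a few sentences in the analysis text; treatment, safety reporting and sample size are unchanged. The downside is that the comparative table of non-serious events omits those reported only to physiotherapists. They remain in the separate listing and in safety oversight.

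### At 6 months the MCID anchor asks about change since the 3-month assessment but is paired with change from baseline

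*Protocol article*

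**What the plan says.** Estimating MCIDs is one of the secondary objectives. Under Secondary outcome measures, "participants will provide a global rating of change score after five measures (6MWD, SR-MWD, WELCH, NEADL and VascuQoL-6) at the 3 and 6-month follow-up assessments". The question printed there is "Has there been any change in your walking ability/walking distance/daily activities etc since the last test". Ratings of −1 to 1 count as no change, 2–3 as a small improvement and 4–7 as a substantial one.

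Under Statistical analysis, "change scores for the five clinical measures will be calculated by subtracting the baseline result from the follow-up results for each participant". These scores then feed three analyses:
- a correlation: "Correlations will be computed for participant self-assessment of performance scores and change in clinical outcomes";
- an analysis of variance across rating groups;
- an ROC curve separating changed (2 or more) from unchanged participants, of which "The data point corresponding to the upper left corner of the curve will represent the MCID".

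The missing-data paragraph confirms that MCIDs are intended at both 3 and 6 months. Table 3 schedules the self-reported measures at all three time points; one row reads "Self-reported maximal walking distance* Self X X X", and WELCH, NEADL and VascuQoL-6 follow the same pattern. The 6-minute walk is scheduled at baseline and 3 months only.

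**The concern.** An anchor-based MCID is meaningful only if the rating and the score describe the same period. At 3 months they do. At 6 months, read literally, the rating starts at month 3 and the score starts at baseline.

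The design makes this matter. MOSAIC is delivered over weeks 1 to 12 and the primary effect is looked for at 3 months, so months 3 to 6 are largely a maintenance period. Someone who gained early and kept the gain truthfully reports no change since month 3 and joins the reference group with a large positive change score. At stake are the 6-month correlations, the group means and the ROC cut-points for four measures, which later trials might reuse.

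**Working it through.** **Periods compared**

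| Visit | Rating covers | Score covers | Match |
|---|---|---|---|
| 3 months | 0–3 | 0–3 | yes |
| 6 months | 3–6 | 0–6 | no |

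The article states no MCID value, so there is no published figure to reproduce.

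**Illustrative size.** No input in this part comes from the document; all are assumptions, in baseline-SD units. They are: a mean gain by month 3 of 0.3 or 0.5 in the MOSAIC arm and none in usual care; SD of true 0–3 change 0.6; mean 3–6 change zero with SD 0.3 or 0.5, independent of the earlier change; error SD in a change score 0.35; rating noise SD 0.3; improvement threshold 0.3. For scale only, the planned 6MWD effect is 58/111 = 0.52 SD.

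Let A = 0.6² + (gain/2)² be the variance of 0–3 change over both arms, B the variance of 3–6 change, E = 0.35² = 0.1225 and R = 0.3² = 0.09. The rating–score correlations are:
- matched over 0–6: (A+B) / √[(A+B+E)(A+B+R)]
- as planned: B / √[(A+B+E)(B+R)]
- matched over 3–6: B / √[(B+E)(B+R)]

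For gain 0.3 and SD 0.3, A = 0.3825 and B = 0.09:
- matched over 0–6: 0.4725/√(0.595 × 0.5625) = 0.82
- as planned: 0.09/√(0.595 × 0.18) = 0.28
- matched over 3–6: 0.09/√(0.2125 × 0.18) = 0.46

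All four combinations, with the simulated ROC cut-points:

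| Gain | SD of 3–6 change | r, matched 0–6 | r, as planned | r, matched 3–6 | Cut-point, matched 0–6 | Cut-point, as planned |
|---|---|---|---|---|---|---|
| 0.3 | 0.3 | 0.82 | 0.28 | 0.46 | 0.37 | 0.31 |
| 0.3 | 0.5 | 0.86 | 0.49 | 0.70 | 0.38 | 0.39 |
| 0.5 | 0.3 | 0.83 | 0.27 | 0.46 | 0.41 | 0.38 |
| 0.5 | 0.5 | 0.86 | 0.48 | 0.70 | 0.43 | 0.51 |

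Repeat simulations reproduce the correlations and move the cut-points by a few hundredths. The area under the curve (AUC) is 0.83–0.86 matched over 0–6, 0.60–0.68 as planned and 0.68–0.77 matched over 3–6.

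The unchanged group's mean change is 0.02–0.05 when matched over 0–6. As planned it is gain/2 = 0.15–0.25, because a 3–6 rating carries no information about the earlier gain.

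**Other assumptions.** A second set used a single population, error SD 0.3 per measurement and threshold 0.5. With mean change 0.5 then 0, and SD 0.6 in each period, A = B = 0.36 and E = 2 × 0.09 = 0.18:
- matched over 0–6: 0.72/√(0.90 × 0.81) = 0.84
- as planned: 0.36/√(0.90 × 0.45) = 0.57

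In that case the cut-point rises from 0.57 to 0.87 and the unchanged mean from 0.10 to 0.50. Over six such patterns the planned correlation was 0.24–0.57 against 0.74–0.84 when matched over 0–6. The cut-point shift ran from −0.10 (0.44 to 0.34) to +0.30, and in one pattern it was almost nil (0.46 to 0.47).

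**The case against.** The strongest reply is that the MCID is the ROC cut-point, and no consistent error in it has been shown. That stands. In some assumed patterns the cut-point barely moves, and in others it moves up or down. A reader might infer that the 6-month MCID is shown to be wrong, or wrong in a known direction; the document gives no trajectories from which to conclude that. A cut-point from a weak anchor is still poorly supported, even where it happens to land nearby.

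Participants might also take the last test to mean baseline, and the printed question is evidently a template whose form versions are not shown. But the article does not define it that way, and its adverse-event item, worded around the last assessment at both follow-ups, favours the previous visit. If participants divided between the two readings, the anchor would mix periods. An unseen analysis plan could define a 3–6 month change, but the article's stated rule is subtraction of baseline.

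Two further inferences go too far:
- Because "The walk test will be completed twice, with the highest 6MWD used for analysis", one might say the 3-month 6MWD rating could refer to the walk done minutes earlier. That is strained: the rating belongs to a follow-up assessment, and the previous-visit reading at 3 months is baseline, which matches the score.
- That the misclassified participants are mostly in the MOSAIC arm follows only from assigning the mean gain to that arm.

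**Conclusion.** The mismatch is in the text and needs no simulation. It is confined to the 6-month anchor-based MCIDs of SR-MWD, WELCH, NEADL and VascuQoL-6. The loss of correlation and AUC appeared under every assumed pattern. The upward shift in the unchanged group's mean requires an average gain by month 3. The size and sign of any shift in the cut-point remain unknown.

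The 3-month MCIDs, the distribution-based MCID (which does not use the rating), the treatment-effect analyses and the sample size of 192 are untouched. No 6-month MCID for 6MWD is possible, because no 6-month walk is scheduled, although the rating text lists 6MWD at both follow-ups. Severity is moderate: one secondary objective is affected, and it is cheaply repaired.

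**What to change.** Preferred: word the 6-month rating as change since the baseline assessment, keep the baseline subtraction, and remove 6MWD from the list of 6-month ratings. This costs a minor form amendment and asks participants to recall a longer period.

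If the forms are already in use, state in the analysis plan that the 6-month rating is paired with 6-month minus 3-month change for the four measures. Both values are already collected, so this is one sentence and no new data. It has a price: fewer improvers, lower precision and a weaker anchor than a true 0–6 month rating (correlation 0.46–0.70 against 0.82–0.86 under the first set of assumptions). It also estimates an MCID for change over months 3 to 6 and should be reported as such. A 0–6 month rating that was never asked cannot be recovered later.
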